#### The psycho-educational component

The patients receive five consecutive nurse consultations every 4 to 6 weeks during the first 6 months after discharge, initiated within the first month. The consultations take place in a quiet setting at the outpatient clinic or by telephone if the patient is unable to visit the hospital, and are performed by cardiology nurses with specific knowledge of patients with heart valve diseases, after a special training module in the psycho-educational intervention. Using a holistic patient view, the aim of the consultation is to improve patients’ coping strategies, disease management, provide information, and help resume daily life after heart valve surgery. The information given is based on national guidelines and standard treatment of patients after heart valve surgery, and will cover disease management including psychological challenges, and the treatment such as technical and medical questions.

The intervention is inspired by R.R. Parse’s *Human Becoming Practice Methodologies* three dimensions [58] interpreted as: (1) discuss and give meaning to the past, present and future; (2) explore and discuss events and possibilities; and (3) move along with envisioned possibilities. According to the theory, three ways of changing health are possible: (1) creative imaging; that is see, hear and feel what a situation might be like if lived in a different way; (2) affirming personal patterns and value priorities; and (3) shedding light on paradoxes, that is, looking at the incongruence in a situation and changing the view held of something. The nurse is present in the process through discussions, silent immersion and reflection, and is able to facilitate contact to or seek advice from a physician if needed. The method of R.R. Parse was chosen to apply a holistic patient approach centred on the individual person’s themes for the consultations. Furthermore, at The Heart Centre at Rigshospitalet, the method is already extensively used in the outpatient heart clinic, such as for patients with inherited heart diseases and adults with congenital heart disease, and fully documented in the COPE-ICD trial [59]. A consultation guide is used to support the consultation (Table 2). Reported issues for patients after heart valve surgery can be: perceiving fragility, sleeping disturbances, body perception, experiencing an information gap after hospital discharge, and for some, symptoms of depression, anxiety and post-traumatic stress disorder, which will all be covered when relevant [17,18].

**Table 2 T2:** The psycho-educational intervention: consultation guide

**Questions**	**Months after surgery**				
	**1**	**2**	**3**	**4**	**5-6**
Discuss the events leading to heart valve surgery. Experiences before, during and after hospital admission.	x				
Address present thoughts and questions.	x	x	x	x	x
How have you been? What has happened since you were here last time?		x	x	x	x
How did you having heart valve surgery affect your life? Are there things/activities you avoid? Do you in any ways feel impaired after having heart valve surgery?		x		x	x
Have you initiated exercise training? How is training going?		x	x	x	
Discuss social network/family. How do they handle the situation? Has anything changed in your social relationships?	x	x		x	x
Has having heart valve surgery affected your work situation? Has it had financial consequences?				x	
Have you had a changed view/perception of your body and its functions?				x	x
How is your health in relation to fatigue, dyspnea, pain, appetite, gastrointestinal function, sleep, sexual functioning, other?			x	x	x
Symptom handling and degree of dyspnea.	x	x	x	x	x
Information/recommendations in relation to discussed issues/problems according to guidelines or if lacking to usual practice.	x	x	x	x	x

### Intervention deviations

Both the experimental interventions and the control intervention will be supervised regularly to assure protocol compliance. Modification of the allocated intervention due to complications of surgery, rehospitalisation or emerging co-morbidities (for example, pneumonia, pericardial exudation, musculoskeletal problems, atrial fibrillation) is always an individual decision, and the time of the measuring of primary outcome (described in section below) at 4 months will be corrected in accordance with changes in the intervention.

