### Objectives

We hypothesise that comprehensive cardiac rehabilitation after heart valve surgery compared with treatment as usual [7,25,26] improves physical capacity (at 4 months) measured by peak VO_2_ (oxygen uptake) by >3 mL/kg/min (primary outcome) [6,10,14,15,20,21,27], and improves self-rated mental health (at 6 months) measured by Short Form 36 (SF-36), the mental health component scale (secondary outcome) by 7 points [28,29]. The reason for choosing separately assessed outcome times is due to the different durations of the two intervention elements; the exercise training is undertaken until 4 months post surgery and the psycho-educational intervention until 6 months post surgery. Further, the physical recovery is expected to be faster than the mental recovery and therefore not comparable.

In exploratory analyses we will assess the effects of integrated rehabilitation *versus* treatment as usual on a 6-minute walk test, heart specific biomarkers (pro-brain natriuretic peptide and copeptin [30]), and echocardiographic measurements (diastolic function (E/A ratio), left atrial size (mm), left atrial volume (mL)) [31,32]. Furthermore, we will assess the effects on time to return to work after valve surgery, and long-term (24 months) employment resignation [5,6,33], healthcare utilisation and mortality [8], and cost effectiveness [33]. Standardised questionnaires: Hospital Anxiety and Depression Scale [HADS] [34], Quality of life Cardiac Version [QoL-CV], EQ-5D [35], Heart Related Quality of Life [HeartQoL R] [36], International Physical Activity Questionnaire [IPAQ] [37], physical activity score and the Emotion and Health Scale [38] will be applied to ascertain numerous exploratory hypotheses concerning the possible effects of rehabilitation on patient perceived physical and mental health.

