### Trial procedure and randomisation

Patient inclusion was initiated on 17 February 2012, and recruitment is currently ongoing. Eligible patients are invited by a nurse or medical doctor to a short consultation on the second or third day after surgery, including distribution of written participant information. Patients needing further time to consider trial participation are contacted by phone 1 week after discharge.

At enrolment, on average 3 to 5 days after surgery, baseline data are collected (Table 1). A 6-minute walk test is performed as close to discharge as possible, using standard guidelines [44]. In case of postoperative complications after enrolment, such as pericardial exudate and atrial fibrillation, the patient’s case will be handled individually, and the intervention will be postponed according to recovery status. Participation in the trial will never delay usual medical follow-up.

**Table 1 T1:** Data collection

	**Baseline**	**1 month**	**4 months**	**6 months**	**12 months**	**24 months**	**Type of data**
*Background*							
Marital status	x						Categorical
Height, weight, body mass index	x						Continuous
*Medical history*							
History of heart disease	x						Binary
Diabetes mellitus	x						Binary
Kidney disease^a^	x						Binary
Chronic obstructive pulmonary disease (COPD)^b^	x						Binary
Hypertension	x						Binary
Dyslipidemia^c^	x						Binary
*Medicine*							
Use of medication, self-reported	x	x	x		x		Categorical
*Heart valve specific questions*							
Type of heart valve disease	x						Categorical
Type of heart valve surgery	x						Categorical
NYHA classification	x	x	x	x	x		Categorical
Left ventricle ejection fraction (LVEF)^d^	x	x	x				Continuous
Euro SCORE II^e^	x						Continuous
Postsurgical complications	x	x					Binary
Postsurgical arrhythmias^f^	x	x	x				Binary
Pacemaker post surgery	x	x	x				Binary
*Clinical measurements*							
Biochemical screening	x	x	x		x		Continuous
ECG		x	x				Binary
Echocardiography		x	x				Continuous
*Physical testing*							
Six minute walk test		x	x		x		Continuous
Cardiopulmonary Exercise Testing		x	x		x		Continuous
Sit and stand test		x	x		x		Continuous
*Questionnaires*							
Level of education	x			x			Categorical
Employment status	x			x			Categorical
Smoking	x			x			Binary
SF-36^g^	x	x	x	x	x	x	Continuous
HADS	x	x	x	x	x	x	Continuous
QoL-CV	x	x	x	X			Continuous
EQ-5D^g^	x			X	x	x	Continuous
HeartQoL	x			X	x	x	Continuous
IPAQ		x	x		x	x	Continuous

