### Control interventions

Both the intervention and the control group will receive usual care. In accordance with current guidelines a cardiologist sees all patients 4 to 6 weeks after heart valve surgery [45,46]. At the follow-up visit a clinical examination, biochemistry and echocardiography are performed. All patients are given general information on anticoagulation and endocarditis prophylaxis. During the trial period the patients will be seen by a physician at The Heart Centre, Rigshospitalet, for the follow-up visit, after 1 and 4 months. All patients are instructed to initiate their usual activities of daily living. Patients in the control group have accepted not to receive local rehabilitation at the hospital or community setting in their written consent.

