### Statistical analysis

SPSS version 17.0 and SAS version 9.3 will be used for the analyses. Data will be pseudo-anonymised and analysed blinded by a trial-independent statistician using intention-to-treat analyses, and a mixed model with repeated measures (MMRM) for continuous outcome measures [75]. Using MMRM ensures that missing data values (in the case of the primary and secondary outcomes) will not create bias as long as the values are missing at random. Two-sided tests are performed. The level of significance is set at 5%. Dealing with multiplicity, gate keeping will be used to adjust the observed *P* values for primary and secondary outcomes [76]. Both unadjusted and adjusted *P* values will be reported.

For the primary and secondary outcome measure, sensitivity analysis will be conducted to assess the potential impact of values missing not at random. For each intervention group (A and B) some quantities (imputing quantities) are computed to be used to impute missing values in a group (A or B) as explained as follows. A comparison between group A and group B where missing values in group A are imputed using imputing quantities obtained from group A and missing values from group B are imputed using imputing quantities obtained from group B is referred to as a best-case analysis. If missing values in group A are imputed using imputing quantities obtained from group B and *vice versa*, the comparison is called a worst-case analysis. The imputing quantities for the primary outcome are the group mean at T1 (X1-bar), the group mean at T4 (X4-bar), the group mean at T6 (X6-bar), the mean difference between the value measured at T4 and that measured at T1 (delta-1), and the mean difference between the value measured at T6 and that measured at T4 (delta-2). The quantities are used to impute missing values in a group (either the same group or the other intervention group) (Table 3). If the standard error (SE) of a parameter estimate calculated using imputed data is smaller than that of the corresponding parameter calculated using complete case data, it is replaced by the latter SE when the *P* value is calculated.

**Table 3 T3:** **The use of imputed values in CopenHeart**_
**VR**
_

**Observed pattern in group B at 1, 4 and 6 months**	**Imputed value in group B at 1 month**	**Imputed value in group B at 4 month**	**Imputed value in group B at 6 months**
mis^a^, mis, mis	X1-bar^b^	X4-bar^c^	X6-bar^d^

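### The primary peak VO2 test may move with individual changes to the allocated intervention, so time since surgery at the test can differ between arms

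*Protocol article*

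**What the plan says.** The Objectives section sets the primary hypothesis at 4 months. Table 1 and the Primary outcome section also give 4 months for the exercise test that follows the 1-month one.

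The Intervention deviations section adds a rule that can move that date. "Modification of the allocated intervention due to complications of surgery, rehospitalisation or emerging co-morbidities" "is always an individual decision", and the time of the primary measurement "at 4 months will be corrected in accordance with changes in the intervention". The Trial procedure and randomisation section shows the direction such a change can take: after postoperative complications, "the intervention will be postponed according to recovery status".

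The arms differ in what there is to change. Under Control interventions, "Both the intervention and the control group will receive usual care", and patients see a physician "for the follow-up visit, after 1 and 4 months". The experimental arm alone also has a supervised 12-week training course starting about 4 weeks after surgery, and a series of nurse consultations.

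**The concern.** The date of the primary test depends on something that happens after randomisation, is judged case by case, and concerns a course that one arm has and the other does not. Whoever modifies an allocated intervention has to know the allocation. A blinded tester protects how the test is conducted and read, but not when it takes place.

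If the rule is followed as written, a rehabilitation patient whose training is put back because of, say, pericardial exudation can be tested later after surgery. For a control with the same complication, the text gives no course whose change would set a new date. The primary comparison could then mix the effect of training with a difference in time since surgery. If patients are still improving without training at that stage, the extra time would count as benefit on the trial's only primary outcome.

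**Working it through.** **1. The plan's own figure.** Sample size and power calculation: difference 3 mL/kg/min, SD 6, type I error 5% (two-sided, from Statistical analysis), power 95%.

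n per arm = 2 × 6² × (1.960 + 1.645)² / 3² = 72 × 12.995 / 9 = 103.96, so 104 by the normal approximation. The t-test version gives 104.93, so 105. The stated 105 per arm is reproduced, and power with 105 is 95.2%. The timing rule does not alter this calculation.

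**2. How little postponement brings the rule into play.** Training starts 4 weeks after surgery and lasts 12 weeks: 4 + 12 = 16 weeks. Four months is 4 × 52/12 = 17.3 weeks. The slack is about 1.3 weeks, so a longer postponement puts the end of a full course beyond month 4. Usual care has two visits and no course end that could shift in this way.

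**3. Possible size.** The article gives no share of patients delayed, no length of delay and no recovery rate. All three are assumed here.

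Bias = recovery per month × (share delayed × delay in the rehabilitation arm − share delayed × delay in the control arm).

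Standard error of the difference = 6 × √(2/105) = 0.828.

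Two-sided type I error = 1 − Φ(1.96 − bias/SE) + Φ(−1.96 − bias/SE).

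With no delay in controls:

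| Share delayed | Delay (months) | Recovery per month (mL/kg/min) | Bias (mL/kg/min) | Share of the target of 3 | Type I error |
|---|---|---|---|---|---|
| 10% | 1 | 0.3 | 0.03 | 1% | 5.0% |
| 20% | 2 | 0.5 | 0.20 | 7% | 5.7% |
| 30% | 2 | 0.5 | 0.30 | 10% | 6.5% |
| 30% | 2 | 1.0 | 0.60 | 20% | 11.2% |

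For the last row, bias/SE = 0.60/0.828 = 0.725, and the two tails are 0.108 + 0.004 = 0.112.

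**4. What shrinks it.** If the average delay in controls is half that in the rehabilitation arm, the second row's bias falls from 0.20 to 0.10 and the type I error to 5.2%. With equal delay in both arms, or no recovery after month 4, the bias is zero. If the 1-month test is also moved, the interval between tests may be preserved and this simple product may misstate the bias, although time since surgery would still differ.

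**The case against.** The best defence is that the rule may be meant for both arms. The paragraph opens by saying that both interventions are supervised, and the allocated intervention can mean usual care as well. Pneumonia or atrial fibrillation could delay a maximal exercise test in a control too. A reader might infer that controls always stay at 4 months, but no passage says so. What stands against this defence is that the shift is tied to changes in the intervention, and usual care as described offers nothing from which a new date would follow. If a symmetric rule is intended, the text needs to say so.

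A reader might also take the bias in favour of rehabilitation as established. The Objectives section says only that "the physical recovery is expected to be faster than the mental recovery", to explain why the two outcomes are assessed at different times. It does not say that peak VO2 is still rising after month 4, and faster physical recovery could equally mean a small slope by then.

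Two further inferences fail. Moving a test date does not breach intention-to-treat, because nobody is excluded or reassigned. Nor can one say how the model would treat a late test. The article specifies "using intention-to-treat analyses, and a mixed model with repeated measures (MMRM) for continuous outcome measures" and does not describe how visit time is coded, a detail that may properly sit in the analysis plan.

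Finally, testing at the end of training is a recognisable choice, since the Objectives section links outcome timing to the length of each intervention component. That is a reason not to insist on a rigid date for everyone, but it does not justify timing that depends on the arm.

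**Conclusion.** The point holds as a defect in a rule the article states, not as an omission. As written, the rule allows time since surgery at the primary test to differ systematically by arm, and it turns a 4-month endpoint into one whose date depends on the course of the intervention.

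Direction and size are not established. A bias towards rehabilitation requires continued recovery after month 4 and less postponement of tests in controls than in rehabilitation patients. Under the assumed ranges the effect runs from negligible (0.03 mL/kg/min) to material (0.6 mL/kg/min, a fifth of the target difference). The intermediate case is modest: 0.20 mL/kg/min and a type I error of 5.7%. Only the upper end of all three assumptions together gives about 11%. The case for acting is that the rule governs the sole primary outcome, that analysis may not fully separate arm from test time afterwards, and that the correction is cheap.

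**What to change.** Replace the sentence that lets the measurement time follow the intervention with one timing rule that does not depend on allocation:

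- Schedule the primary exercise test at 4 months from one named anchor, within the same window in both arms. The anchor needs stating, because the Objectives section counts from surgery and the exploratory outcomes are counted from randomisation.
- Where complications require the test to be delayed, apply the same complication-based test-delay rule to both arms.
- Record the actual date of every exercise test, including those already done, and add a sensitivity analysis of the primary outcome using actual time since surgery.
- Treat any additional test at the end of a delayed training course as supportive only.

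The cost is a short amendment and a scheduling instruction. Some delayed patients may be tested before they complete training, so the estimated effect may be slightly smaller. The sample size does not change. When training starts or is postponed remains a clinical decision that this change does not affect.

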### Outcomes and data collection

#### Primary outcome

Physical capacity is measured after 1 and 4 months by peak VO_2_ using cardiopulmonary exercise testing (Ergo-Spiro CS-200, Schiller, Switzerland), and is performed in accordance with current guidelines [60]. An ergometer bicycle is used, monitoring heart rate, blood pressure, ECG and gas exchange during workload and in the recovery period. Optimal test duration is 8–10 min with a pre- and post-test phase of 2–4 min. Gas, volume and ambient calibration are performed before each session to address changes in room temperature, humidity and air O_2_ content. A ramp protocol is used with initial workload of 25 or 50 watts, increasing by 12.5 watts/min gradually until exhaustion. Exhaustion is evaluated by a respiratory exchange ratio (RER) ≥1.10, reach of anaerobic threshold [60], or the patient’s subjective exhaustion. The peak V0_2_ is determined after standard definitions [60] as the highest V0_2_ measured during the test.

The person who performs the test is either a medical doctor or a nurse with cardiology patient experience. To equally encourage patients independent of the person present, a guide has been developed by the research group, and regular supervision of each tester by a primary investigator is maintained. For safety reasons, criteria for an early test termination have been defined.

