Intensive physical exercise regimen. Physical exercise is initiated at a physiotherapist supervised setting at the Heart Centre, Rigshospitalet, 4 weeks after surgery to ensure optimal healing and decrease the risk of unstable sternum. Using wireless electrodes integrated into t-shirts (Corus-Fit, CardioCardio and Corus Exercise Assistant, version 2.0.16, Finland) potential cardiac arrhythmias, electrocardiographic abnormalities such as ST segment changes, T-wave alterations, atrial or ventricular arrhythmias, and training intensity level are monitored. The training is initiated with one to three mandatory exercise sessions in the primary investigating hospital, Rigshospitalet. Subsequently, the patients can choose to continue the intensive physical exercise regimen either in hospital at Rigshospitalet, at a local CopenHeart-certified facility, supervised by physiotherapists, or as supervised home-based training. Supervised home-based physical training has previously shown similar results to hospital-based training [52]. This finding has been confirmed in a Danish setting [53]. An exercise bicycle at home is required for the patient to perform home-based exercise training.

The training programme continues for 12 weeks, comprising three sessions weekly of 60 min, 36 sessions in total. The training protocol consists of cardiovascular training and strength exercises due to the fact that decreased exercise intolerance in heart valve patients has been suggested to depend on decreased muscular strength [54].

One session consists of 10 min warm-up bicycling, 20 min bicycling with increased intensity (cardiovascular training), 20 min strength exercises, and 10 min stretching and cool-down period. The warm-up session is performed at the intensity of 11–12 on the Borg scale [55]. The 20-min cardiovascular training is performed as interval training. Each session is divided into three sections. Each section contains intensity 13–17 on the Borg scale and time limit (2–15 min) varying between each section; the second section with longest and highest intensity. A cool down period of 5 min is included after the 20 min of cardiovascular training.

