### Sample size and power calculation

We are performing a randomised trial with the continuous variable VO_2_ peak from independent control and intervention group participants as primary outcome with one control per intervention group participant. Previous studies report that VO_2_ peak is normally distributed in the intervention and control groups with a standard deviation between 4.0 and 9.3 mL/kg/min [14,15,20,21], though this might depend on the baseline peak VO2. However, if the true difference between the intervention and control group mean is 3 mL/kg/min [14,15,21], and the standard deviation is 6 mL/kg/min, inclusion of 105 participants is needed in the experimental intervention group, and 105 in the control group (a total of 210 participants) to be able to reject the null hypothesis, stating that the mean in the intervention and the control groups are the same with a power of 95%, and a type I error probability of 5%.

The secondary outcome measure is the continuous variable ‘mental health’. If the true difference between the intervention and control group is 7 points, and the standard deviation is 18 points [28,29], we will be able to reject the null hypothesis that the population means in the intervention and control group are equal with a probability of 80%, and a type 1 error probability of 5%.

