## Discussion

The major strength of The CopenHeart_VR_ is that it includes consecutive patients with a reasonable number of inclusion and exclusion criteria securing external validity for the results. The trial employs central, stratified randomisation, which secures against selection bias [77-79]. The primary outcome is assessed blinded to intervention, and so are all statistical analyses, which should reduce detection and interpretation bias [77-79]. The long-term outcomes are based on registry data, which are also likely not to include significantly biased reporting of outcomes.

The secondary outcome of self-assessed mental health is by nature subjective, and is likely to be biased [77-79]. The patients answer questionnaires independently of the researchers. All questionnaires are distributed electronically, thus data management is handled independently from the researchers that interpret data. All data are stored electronically in a coded database, and in an independent spread sheet, only accessible for the CopenHeart Group. The exploratory outcome measures highly impact the importance of this study as very limited knowledge exists concerning social and community outcomes for this patient group.

The limitations of the trial and methods used are similar to those of other trials including physical exercise and physical testing, which are time-of-day, and day-to-day variation in exercise testing [80]. To ensure standard testing of all physical exercise tests in the trial, standardised instructions for patients have been developed as described in the methods section. Including trial patients with left- and right-side heart valve surgery will result in an inhomogeneous trial population. Also, as peak VO2 is dependent on exercise capacity, age or recovery capacities, which differ according to the valve involved, consequently the expected results are going to depend on the recruitment. Conversely, the trial population will be representative of the broad heart valve population, and facilitate the external validity of The CopenHeart_VR_ rehabilitation programme in terms of daily clinical practice.

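### The primary exercise test accepts the anaerobic threshold, a submaximal point, as sufficient evidence of exhaustion, so peak VO2 can include submaximal tests and effort should be shown by arm

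*Protocol article*

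**What the plan says.** The Primary outcome section of the protocol article describes a bicycle ramp with workload "increasing by 12.5 watts/min gradually until exhaustion". The next sentence says how exhaustion is judged: "Exhaustion is evaluated by a respiratory exchange ratio (RER) ≥1.10, reach of anaerobic threshold [60], or the patient’s subjective exhaustion". Peak VO2 is then taken "as the highest V0_2_ measured during the test". No minimum effort is attached to that value there or elsewhere in the article.

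Two safeguards are stated. The same section says: "To equally encourage patients independent of the person present, a guide has been developed by the research group", and adds regular supervision of each tester. The Discussion says: "The primary outcome is assessed blinded to intervention, and so are all statistical analyses".

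Patients cannot be blinded. Under Control interventions: "Patients in the control group have accepted not to receive local rehabilitation at the hospital or community setting in their written consent". The experimental arm is offered 36 sessions over 12 weeks, each with a 20-minute interval-cycling block at Borg 13 to 17 (The physical exercise component).

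**The concern.** The stated objective is physical capacity. Peak VO2 measures capacity only so far as the patient is taken close to maximal effort. In an incremental test the anaerobic threshold is reached before peak effort. It marks a stage of the test and is not a sign that the patient is exhausted. As worded, a test ended shortly after it satisfies the exhaustion criterion, and whatever VO2 was highest by then counts as peak.

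Two consequences are possible. If submaximal tests are equally common in both arms, the effect is diluted and the outcome becomes noisier. If they are more common in one arm, the between-arm difference includes a difference in effort. The second is plausible here because patients know their arm and only one arm trains repeatedly at high exertion on a bicycle, the test device. Blinding testers and analysts does not reach a patient's own decision to stop.

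**Working it through.** **Step 1. The rule as written.** The criteria are RER ≥1.10, or threshold reached, or subjective exhaustion. Any one suffices. A patient whose RER has reached 1.10 will ordinarily have passed the threshold already, so the RER branch admits hardly any test that the threshold branch does not. That the threshold comes before peak effort is general exercise physiology. The guideline that the protocol cites at this point could not be consulted.

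**Step 2. When patients learn their arm.** Randomisation follows baseline data collection, with enrolment on average 3 to 5 days after surgery (Trial procedure and randomisation). The first cardiopulmonary test is at 1 month (Table 1). Both the 1-month and 4-month tests are therefore done after allocation.

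**Step 3. The plan's own figure.** Inputs from Sample size and power calculation: difference 3, SD 6, power 95%, type I error 5%. Statistical analysis specifies two-sided tests.

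n per arm = 2 × (1.96 + 1.645)² × 6² / 3² = 103.97, so 104. The t-test version gives 104.93, so 105. The planned 210 is reproduced, and power at 105 per arm is 95%. The sample size is not in question.

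**Step 4. Unequal effort (illustration).** The documents give neither the share of submaximal tests nor their shortfall, so both are assumed.

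Shift in estimate = shortfall × difference in share

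| Shortfall (mL/kg/min) | 5 points | 10 points | 20 points |
|---|---|---|---|
| 2 | 0.1 | 0.2 | 0.4 |
| 4 | 0.2 | 0.4 | 0.8 |
| 6 | 0.3 | 0.6 | 1.2 |

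The range 0.1 to 1.2 is 3% to 40% of the target of 3. The standard error at 105 per arm is 6 × √(2/105) = 0.828. With no true effect, a shift b gives a two-sided rejection rate of P(Z > 1.96 − b/0.828) + P(Z < −1.96 − b/0.828):

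- b = 0.1 gives 5.2%.
- b = 0.2 gives 5.7%.
- b = 1.0 gives 23%.
- b = 1.2 gives 31%.

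The sign follows whichever arm has more submaximal tests. An excess among controls favours the intervention, and an excess in the experimental arm works against it.

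**Step 5. Equal effort (illustration).** Assume that a share p of 10 to 30% in both arms reads a fraction f of 0.6 to 0.8 of true peak, with a true mean of 20 mL/kg/min.

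Effect = 3 × (1 − p + pf); variance = 36 + p(1 − p) × [(1 − f) × 20]²

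- p = 0.1, f = 0.8: effect 3 × 0.98 = 2.94; SD √(36 + 0.09 × 16) = 6.12; power 94%.
- p = 0.3, f = 0.6: effect 3 × 0.88 = 2.64; SD √(36 + 0.21 × 64) = 7.03; power 78%.

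This keeps the spread at 6 among submaximal tests. If their spread shrinks in proportion, the first variance term becomes 36 × (1 − p + pf²). At p = 0.3, f = 0.6 that gives 36 × 0.808 + 13.44 = 42.5, SD 6.52 and power 84%. In both versions the loss is attenuation and noise, and no spurious benefit arises.

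**The case against.** The strongest reply is that the text sets no stopping rule at the threshold. The ramp runs to exhaustion, testers follow an encouragement guide and are supervised, and no sentence accepts or rejects a test. A reader might infer that testers stop patients at the threshold, or that clearly submaximal tests are being admitted in numbers. The article does not say so, and the guide suggests that many tests go further. This part of the reply stands.

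It is also true that unequal effort can affect any symptom-limited test in an exercise trial, and that deleting the threshold would leave subjective exhaustion as a sufficient criterion. The deletion therefore cannot guarantee maximal tests, which is why the effort summary belongs with it. Both arms also take the same bicycle test at 1 month, before training begins, so controls are not new to the device at 4 months. That narrows the route to unequal effort without closing it.

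A reader might further infer that the trial has no check on effort. That cannot be concluded either. A summary of RER by arm may sit in a full protocol or an analysis plan that is not shown, and its absence from a journal article is not the complaint.

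What the reply does not answer is the wording itself. The article lists the threshold as evidence of exhaustion in the definition of its primary outcome, and nothing elsewhere in it corrects this.

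**Conclusion.** The point holds as a defect in the primary outcome definition: a submaximal landmark is sufficient evidence of exhaustion, which leaves the RER criterion with little discriminating value. That rests on the article's wording and on the ordering of threshold and peak effort.

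The consequence is a risk of unknown size. The illustrative shift of 0.1 to 1.2 mL/kg/min, against "if the true difference between the intervention and control group mean is 3 mL/kg/min", depends wholly on assumed shortfalls and assumed differences in share, and its direction is assumed too. Equal submaximal effort would instead lower the effect to between 2.94 and 2.64, with power between 94% and 78% on the assumptions shown. Neither illustration isolates what the threshold clause adds beyond the subjective criterion.

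It is tempting to go further and say that the trial's effect mixes effort with capacity, or that a positive result could not be attributed to capacity. The documents do not support that, because they report no effort data and do not show that effort differs by arm. The change is worth making because it is cheap and lets readers judge the matter.

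**What to change.** 1. In the primary outcome definition, remove reaching the anaerobic threshold as a criterion of exhaustion. The safety criteria for early test termination are a separate matter and are not affected.
2. Because subjective exhaustion alone still suffices, summarise peak RER and the share of tests with RER ≥1.10 by arm at 1 and 4 months.
3. Keep all tests in the intention-to-treat primary analysis, whatever their RER. Selecting on RER after randomisation would break the comparison.
4. Add VO2 at the anaerobic threshold from the same test as one supportive, less effort-dependent analysis, and read it beside the primary result before attributing that result to capacity.

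The cost is one wording change, one table and one supportive analysis. Gas exchange is already monitored at each test, so no visit or measurement is added. The downside is that some tests will be shown to be submaximal.
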